### Randomization and blinding

All participants eligible to take part will be randomized to the E-care 4 caregivers intervention or the WLC group, stratified by their scores on the K10 using a cutoff score of 20 [19]. The random allocation sequence and the randomization process will be performed by an independent researcher in the Random Allocation Software program. Due to the nature of the intervention, double-blinding of group allocation is not possible.

### Intervention: E-care 4 caregivers

The online self-management course comprises eight modules. The elements of it are described in Table 1. The modules include theory, exercises, examples of caregivers` experiences, and short videos. This intervention will include personalized feedback provided by a coach and a diary app. An Internet forum that is developed as a closed group on Facebook will also be a part of the online course. This forum is used for peer contact and is moderated by a coach.

**Table 1 Tab1:** Content online intervention

Themes	Topics	Goals
1. What is depression?	Psychoeducation concerning symptoms, diagnosis, types, and causes of, as well as treatment options for, depression	To familiarize caregivers with the nature of the depressive disorder and its treatment to enable recognition of symptoms
2. Implications of depression for the caregiver	Emotions that can arise for the caregiver and the family, grief processes that occur, and practical implications of the depression	To recognize, validate, and accept negative emotions that can arise in a caregiver when facing the situation that a loved one has depression
3. How to think differently	Automatic thoughts, cognitive distortions, and how to correct these using principles of cognitive therapy	Using cognitive principles to recognize dysfunctional thoughts and change them to help caregivers in this stressful situation
4. Signaling stress and burnout	Psychoeducation about causes and signs of stress using the capabilities/workload model	Recognition and/or prevention of symptoms of overburdening and stress
5. Caring for yourself	Tips to better take care of yourself and your own boundaries with exercises about help-seeking, assertiveness, time-management, and relaxation exercises	Preventing and/or decreasing symptoms of overburdening and stress via various exercises
6. Learning to communicate better	Psychoeducation about communicating with someone with depression using the disarm technique and principles of emotionally focused therapy	To recognize your own role in communicating while understanding someone with depression better to avoid constant repetitive arguments
7. Coping with suicidality	Psychoeducation about suicidality, tips to communicate about suicidality, establishing and following safety procedures	Empowering caregiver with more knowledge about suicidality and safety measures as well as gaining more confidence in communication and setting boundaries
8. Caring for children of a parent with depression	Psychoeducation about possible consequences for the children of a parent with depression, with tips for communication, structure, and referral possibilities	Support parents to raise their children to become emotionally balanced individuals within a challenging environment where one parent has depression

#### Development of the intervention

The online self-management intervention is based on the self-help book *Depression: a guide for family members* [20]. This book is based on psychoeducation, CBT principles, and the experience of the book’s author in working with support groups for family members of depressed people.

Relevant stakeholders were also included in the early development phase of the intervention by means of two focus groups in which the needs of nonprofessional caregivers were assessed. The first focus group included five nonprofessional caregivers currently caring for a loved one with depression. The second focus group consisted of eight professionals in the field of depression, nonprofessional caregivers, and/or professionals in the design and use of Internet interventions.

#### Content

Both caregivers and experts agreed that the focus of the content should be on the caregiver, not on the patient with depression. Key components are recognition and validation for the nonprofessional caregiver. Psychoeducation about depression, stress, burnout, and self-care is needed, as well as practical information about general mental health care and tips regarding communication, grief, assertiveness, boundaries, and how to cope with negative feelings (guilt, responsibility, anger). Optional information for certain situations would be about coping with suicidality, changes in a relationship, and how to support children of a parent with depression.

#### Format

Both caregivers and experts preferred a cherry-picking design of the intervention (i.e., caregivers can choose which modules they would like to follow). Both groups agreed the content should be visually attractive and informal in tone, yet professional. Information should be provided by experts in an interactive manner by using text, videos, exercises, and examples. Interestingly, the caregivers differed in their recommendations about the frequency of use. Professionals preferred a more structured form, whereas nonprofessional caregivers recommended that the online course be available whenever they could find the time. Also, caregivers highly valued professional guidance by a coach, as they require validation and recognition of their stressful situation. The opportunity for peer contact would also be highly advisable.

#### Prerequisites

Both focus groups agreed that the online intervention should also be accessible via smartphones and tablets. Furthermore, it should be free of charge, password-protected, and run without technical difficulties. Also, it would be beneficial if participants could track their own progress to feel a sense of accomplishment.

### Assessments

All quantitative assessments are self-report measures and will be administered online. Semistructured qualitative interviews will be conducted by telephone. An overview of the questionnaires and their time of assessment is provided in Table 2.

**Table 2 Tab2:** Overview of questionnaires and the time of assessment

Questionnaire	Baseline	6 weeks
Demographic variables, participant + depressed family member	X	
Kessler Psychological Distress Scale (K10)	X	X
Generalized Anxiety Disorder Scale (GAD7)	X	X
Zarit Burden Interview (ZBI-12)	X	X
Euro-Qol (EQ-5D)	X	X
System Usability Scale (SUS)		X
Pearlin Mastery Scale	X	X

### Feasibility instruments

The qualitative analysis to determine feasibility will be carried out using a structured telephone interview after subjects complete the online self-management course. In-depth interviews about what was experienced as valuable in the course, missing and redundant elements, and user-friendliness will be held with nonprofessional caregivers. Questions will also be asked regarding how well the course fits in with and contributes to their everyday lives and how they use the course to decrease their own burden. A topic list will be used that is based on the outcomes of the focus groups. The interview will start with the ‘grand tour question’: “What was your experience in using the online course?” The interviews will last between 45 minutes and 1 h and will be recorded for analysis.

#### User-friendliness

The user-friendliness of the online intervention is measured using the Dutch version of the System Usability Scale (SUS) [21]. The SUS is composed of 10 statements that are scored on a 5-point scale of strength of agreement. Final scores for the SUS can range from 0 to 100, where higher scores indicate better usability. This means that products that are at least passable have SUS scores above 70, with better products scoring in the high 70s to upper 80s. Truly superior products score better than 90. Products with scores less than 70 should be considered candidates for increased scrutiny and continued improvement and should be judged to be marginal at best. Reliability is good (Cronbach’s α 0.91).

### Initial effects instruments

#### Primary outcome measure

##### Psychological distress

Psychological stress will be measured by the translated ten-item version of the Kessler Psychological Distress Scale (K10) [22]. The K10 consists of ten items concerning feelings of depression, anxiety, and insecurity experienced in the last month. Subjects can score these feelings on a 5-point Likert scale (5 = “all of the time” to 1 = “none of the time”); the total score ranges from 10 (no distress) to 50 (severe distress). The reliability (Cronbach’s α) of the Dutch K10 was 0.94, and its validity was good (AUC 0.87). With a cutoff point of 20, the Dutch K10 reached a sensitivity of 0.80 and a specificity of 0.81 for any depressive and/or anxiety disorder [19].

#### Secondary outcome measures

##### Anxiety symptoms

Anxiety symptoms will be measured using the Dutch version of the 7-item Generalized Anxiety Disorder Scale (GAD7) [23]. The GAD7 consists of seven items concerning anxiety complaints experienced in the last 2 weeks. Subjects can score these feelings on a 4-point scale (0 = “not at all” to 3 = “nearly every day”); total score ranges from 0 to 21. With a cutoff point of 12, the web-based Dutch version is reliable and has a sensitivity of 0.83 and a specificity of 0.65 for generalized anxiety disorder [24].

##### Subjective burden

Subjective burden is measured with the Dutch version of the Zarit Burden Interview [25]. This questionnaire measures the consequences of long-term psychiatric or physical illnesses of patients on their nonprofessional caregivers. It consists of 12 items that are scored on a 5-point scale (0 = “never” to 4 = “almost all the time”); total score ranges from 0 to 48. Bedard and colleagues [26] found a Cronbach’s α greater than 0.88 for the overall scale and high values for the personal strain factor and the role strain factor (0.89 and 0.77, respectively).

##### Quality of life

Quality of life will be measured using the five-item self-report instrument EQ-5D [27]. The EQ-5D measures health-related quality of life and consists of five dimensions (mobility, self-care, main activity, pain, and mood). Each dimension is rated as causing “no problems,” “some problems,” or “extreme problems.” The EuroQol valuations appear to have good test-retest reliability. The EQ-5D thus distinguishes 486 unique health states. Each unique health state has a utility score that ranges from 0 (poor health) to 1 (perfect health). We used the single EQ-5D summary index score.

##### Perceived control

Perceived control of events and ongoing situations will be assessed using a five-item version of the Pearlin Mastery Scale [28] regarding how much control an individual perceives having over circumstances in his or her life. The scores per item vary from 1 (totally disagree) to 5 (totally agree). The Pearlin Mastery Scale has good psychometric properties and shows good reliability. Items are summed for a total mastery score (range from 5 to 25), with higher scores indicating greater perceived control (internal locus of control).

##### Other questions: general demographic characteristics

Information on general demographic variables such as age, sex, marital status, medication use, income, hours spent on caregiving, and educational level will be collected at baseline. Also, demographic variables related to the caregiver’s loved one are gathered, including age, sex, type of relationship, living situation, diagnosis, comorbidity, treatment, and suicidality.

### Analysis

#### Qualitative evaluation

Qualitative interview data will be analyzed using thematic content analysis [29]. The recorded interviews will be processed verbatim. Different themes will be identified and described using grounded theory principles [30]. The quality of the data collection will be guarded by a process of peer debriefing. Participants will be selected via purposive sampling on demographic variables (age, sex, type of relationship with the patient). Deviant cases will be actively searched for using information on the Internet forum or on the basis of SUS scores. Participants will be included until data saturation is reached.

#### Statistical analysis

Descriptive statistics will be used to report demographic variables, clinical outcomes, and the use of the different modules. The analysis of the quantitative primary and secondary measures will be performed on an intention-to-treat basis. To test the robustness of the findings, we will also conduct per-protocol analyses (those who completed the baseline and 6-week assessments and followed at least 50 % of the modules). Comparisons will be made between- and within groups for pre- and posttest measurements. For the intention-to-treat analyses for the continuous variables, repeated measures analysis of variance will be used. Standard effect sizes will be calculated (Cohen’s *d*) with confidence intervals. Sensitivity analyses will be performed on the primary outcome psychological distress (K10 score). IBM SPSS version 21 software (IBM, Armonk, NY, USA) will be used in analyses.

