## Methods/design

This study is a two-arm randomized controlled trial (RCT) comparing the online intervention E-care 4 caregivers with a wait list control group (WLC). Assessments will be done at baseline and 6 weeks later.

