#### Sample size

There are no definitive guidelines for sample sizes of pilot studies. On the basis of a simulation study [18], a sample size of 70 participants is recommended to estimate pooled standard deviations for a continuous variable. Taking into account an attrition rate of 20 %, we will include 84 respondents in total.

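### The repeated measures ANOVA is a valid contrast but adjusts for neither baseline nor the K10 stratum, and within-group comparisons stand unranked beside it

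*Protocol article*

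**What the plan says.** Three parts of the protocol article bear on this.

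- **Method.** Under Statistical analysis: "For the intention-to-treat analyses for the continuous variables, repeated measures analysis of variance will be used". No covariate is named. Cohen's d with confidence intervals is promised, without saying which contrast it standardises.
- **Comparisons.** The same section says: "Comparisons will be made between- and within groups for pre- and posttest measurements". Nothing states which of the two carries the inference, or that the within-group part is descriptive.
- **Design.** Methods/design sets two time points: "Assessments will be done at baseline and 6 weeks later". Under Randomization and blinding, participants are allocated "stratified by their scores on the K10 using a cutoff score of 20". The K10 is also the primary outcome, so the stratification factor is the primary outcome's own baseline, dichotomised.

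The Discussion limits the effectiveness results to preliminary conclusions.

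**The concern.** With two time points, the arm-by-time test of a repeated measures ANOVA is a t-test on raw change scores. In a randomised trial, analysis of covariance (ANCOVA) of the 6-week score on the baseline score estimates the same effect with smaller variance. The allocation is balanced on baseline K10, but an analysis that leaves K10 out does not credit that balance to its standard error.

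The second part concerns interpretation. A pre-post comparison within one arm has no control. Any shift over 6 weeks that both arms share appears in it, and a significant change in the intervention arm beside a non-significant one in the wait list group is easily taken for an effect.

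A small pilot that promises an initial effect with a confidence interval would therefore report wider intervals than its data require, and would put an uncontrolled comparison beside the randomised one.

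**Working it through.** **Inputs.** The Sample size section starts from 70 ("a sample size of 70 participants is recommended to estimate pooled standard deviations for a continuous variable") and allows 20% attrition. 70 × 1.20 = 84 reproduces the stated total. 84 × 0.80 = 67.2, so about 33 completers per arm if allocation is 1:1 (the ratio is not stated). The article gives no correlation r between baseline and 6 weeks, no SD and no target effect. I assume equal SD s at both times and r = 0.5 to 0.7.

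**Step 1: change score against ANCOVA, ignoring stratification.** With n per arm:

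- Var(change contrast) = 2(1−r)s² × 2/n
- Var(ANCOVA) = (1−r²)s² × 2/n
- Variance ratio, ANCOVA to change = (1+r)/2
- Ratio of reported interval widths, change to ANCOVA = √(2/(1+r))

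| r | (1+r)/2 | Variance loss | Interval width ratio |
|---|---|---|---|
| 0.5 | 0.75 | 25% | 1.15 |
| 0.6 | 0.80 | 20% | 1.12 |
| 0.7 | 0.85 | 15% | 1.08 |

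Over r = 0.3 to 0.9 the variance loss runs from 35% to 5%. For illustration, at r = 0.6 and an assumed d of 0.5 with 33.5 per arm, power is 62% for the change score and 71% for ANCOVA.

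**Step 2: K10 under the stratified randomisation.** The variance of a change score, in units of s², splits into (1−r)², which comes from baseline, and (1−r²), which does not. ANCOVA removes the first part. Stratifying on K10 already shrinks its contribution to the between-arm contrast to v(1−r)², where v is the share of baseline variance left within strata. For a normal baseline cut at its median, v = 1 − 2/π = 0.363. Where a K10 of 20 falls in this population is not stated, so the median is an assumption.

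| r | Actual change-score variance: 0.363(1−r)² + (1−r²) | ANCOVA: 1−r² | True loss | Variance the ANOVA reports: 2(1−r) |
|---|---|---|---|---|
| 0.5 | 0.841 | 0.750 | 11% | 1.000 |
| 0.6 | 0.698 | 0.640 | 8% | 0.800 |
| 0.7 | 0.543 | 0.510 | 6% | 0.600 |

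Simulation of stratified trials agrees: the true loss is about 5-11% with the cut at the median, and up to about 13% with the cut at the lower quartile. The reported variance exceeds the actual one, so the reported intervals remain 8-15% wider than ANCOVA's, and type I error at a nominal 5% falls to about 3.4-3.7% (3.3-4.3% across other simulated settings). Once continuous baseline K10 is in the model, adding the stratum term gains nothing measurable for K10.

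**Step 3: secondary outcomes.** Stratification balances K10 only. For anxiety, burden, mastery and EQ-5D it helps only as far as their baselines correlate with K10, so Step 1 gives the upper limit: 15-25% of variance at r = 0.5 to 0.7.

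**Step 4: within-group tests when the arms do not differ.** Let both arms improve by g SD. A paired t-test with m = 33 has noncentrality g√m / √(2(1−r)). With p its chance of significance, the intervention arm alone is significant with probability p(1−p), which cannot exceed 0.25.

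| Shared shift g | r | p | p(1−p) |
|---|---|---|---|
| 0.1 | 0.5 to 0.7 | 0.09 to 0.11 | 8-10% |
| 0.3 | 0.6 | 0.46 | 25% |
| 0.5 | 0.5 | 0.80 | 16% |
| 0.5 | 0.7 | 0.95 | 5% |

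**The case against.** The strongest reply is that a randomised comparison is already planned. The text names between-group comparisons, an intention-to-treat basis and "repeated measures analysis of variance will be used"; the arm-by-time term is unbiased, and its error for K10 is on the conservative side. That stands. A reader might infer that the plan replaces the between-arm contrast with pre-post tests, or that the ANOVA itself lets uncontrolled change count as an effect. The article supports neither: shared change cancels in the arm-by-time term and enters only through the within-group comparisons.

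Three further points stand in part.

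- A reader might carry the 15-25% loss over to K10. That formula assumes unstratified randomisation, so for K10 it overstates the true loss. It does describe the excess in the variance that the ANOVA would report.
- A reader might quote a 50% chance that exactly one arm is significant. That is 2p(1−p) near its maximum, and half of it is the wait list arm alone, which nobody would read as benefit. Nor does the article say it will claim an effect from one arm's significance. The risk comes from the missing ranking, not from a stated rule.
- The Study population section sets no distress threshold for entry, so strong regression to the mean cannot be presumed. The shared shift in Step 4 is an assumption.

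Finally, the trial is sized to estimate a pooled SD rather than for power, and its conclusions are preliminary. That lowers the stakes. It does not favour an unadjusted interval when the baseline values are already collected. An unseen analysis plan may add detail, but the method and the paired comparisons are fixed in this text.

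**Conclusion.** The point holds as one of efficiency and ranking, not of validity. The planned analysis leaves out both the baseline value and the factor used to stratify randomisation, and it places uncontrolled comparisons level with the controlled one.

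At an assumed r of 0.5 to 0.7, the cost for K10 is reported intervals about 8-15% wider than with baseline adjustment and a conservative test (about 3.4-3.7%), against a true sampling-variance loss of about 5-11%. For secondary outcomes the variance loss is up to 15-25%. If both arms improve equally, the intervention arm alone can appear significant in up to about 25% of trials, and in about 5-16% at shared shifts of 0.1 or 0.5 SD.

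These sizes rest on the assumed r, equal SDs at both times, about 33 completers per arm and, for the K10 figures, a cutoff near the median. The direction does not depend on them for any r below 1. The change is worth making, but the trial is not compromised without it.

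**What to change.** In the Statistical analysis section:

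1. Define the effect estimate for each continuous outcome as the between-arm difference at 6 weeks, adjusted for that outcome's continuous baseline and for the K10 randomisation factor, with a 95% CI. For K10 itself, continuous baseline K10 suffices and the stratum term is optional.
2. Derive Cohen's d and its interval from that contrast.
3. Report within-group changes descriptively only, without tests or claims of effect.

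The cost is wording. Table 2 shows every outcome for which an effect is to be estimated collected at both time points, and baseline K10 is already used for the randomisation. No extra data, visits or participants are needed.

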**Methods/design:**

The study is a randomized controlled trial in which we are comparing the E-care 4 caregivers online intervention with a wait list control group. Eighty-four nonprofessional caregivers of patients with depression aged 18 years or older are being recruited from among the general population. Feasibility is determined by semistructured telephone interviews evaluating the subjects’ satisfaction with the intervention and by using a questionnaire on the user-friendliness of the system. The primary outcome measure used to examine the initial effects of the intervention is psychological distress. Secondary outcome measures are subjective burden, symptoms of anxiety and depression, level of mastery, and quality of life. Assessments will be done at baseline and 6 weeks later. Statistical analysis of the effects of the intervention will be carried out on the basis of the intention-to-treat principle.

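### The method named for the intention-to-treat analysis, repeated measures ANOVA on two time points, uses only people with both scores unless missing values are imputed first, which the article does not state

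*Protocol article*

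**What the plan says.** The protocol article states the principle twice. The abstract (Methods/design) says: "Statistical analysis of the effects of the intervention will be carried out on the basis of the intention-to-treat principle". The Statistical analysis section says: "The analysis of the quantitative primary and secondary measures will be performed on an intention-to-treat basis". That section then names the method: "For the intention-to-treat analyses for the continuous variables, repeated measures analysis of variance will be used". It gives no rule for a missing 6-week score.

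The design has two measurement occasions: "Assessments will be done at baseline and 6 weeks later". The Sample size section expects loss: "Taking into account an attrition rate of 20 %, we will include 84 respondents in total".

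The robustness check is a per-protocol analysis of "those who completed the baseline and 6-week assessments and followed at least 50 % of the modules". Sensitivity analyses on the K10 are also promised, but their content is not described and they are not tied to missing data.

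**The concern.** Standard repeated measures ANOVA takes one complete row per person. With two occasions, anyone without a 6-week score leaves the analysis, and their baseline score goes too. The article therefore promises one principle and names a method that, as written, does not deliver it. Participants stay in the arm to which they were randomised, but the set shrinks to those who completed the 6-week assessment.

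Two things are at stake. First, the planned per-protocol comparison loses its use as a check on dropout, because both sets would leave out the same people. Second, an analysis of change scores in completers is biased when dropout depends on baseline distress to a different extent in the two arms, even if data are missing at random given baseline. Different dropout by arm is possible here: wait-list participants receive the course only after the 6-week assessment, while the intervention arm already has it. The effect sizes with confidence intervals come from this analysis, and the Discussion expects the pilot to inform the size of a later trial.

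**Working it through.** **Inputs from the article.** Target 70, attrition 20%, total 84 (Sample size); two assessments (Methods/design and Table 2); repeated measures ANOVA for intention-to-treat, and the per-protocol definition (Statistical analysis).

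**1. The plan's own figure.** 70 × (1 + 0.20) = 84, which reproduces the stated total. Dividing instead, 70 / (1 − 0.20) = 87.5, would round up to 88. That is a separate matter and nothing below depends on it.

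**2. People analysed at the planned attrition.** 84 × 0.80 = 67.2 have both scores; 84 × 0.20 = 16.8 do not. So about 67 are analysed and about 17 are left out.

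**3. What the ANOVA tests.** With two occasions, the group-by-time F equals the squared two-sample t on the change score. In one simulated data set of 84 with 17 missing 6-week scores, the analysis used 67 people, and both F and t² were 1.3046. The 17 contributed nothing.

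**4. The two analysis sets side by side.**
- Intention-to-treat, as the named method delivers it: both assessments present.
- Per-protocol: both assessments present and at least 50% of modules followed.

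The only difference is the module rule.

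**5. Size of possible bias (illustration).** Assumptions, none of them from the article: equal allocation, no true effect, scores in SD units, pre-post correlation r = 0.6, and log-odds of dropout rising by 1 per baseline SD in any arm with dropout. With no true effect, the expected 6-week score given baseline b is r × b, so the expected change is (r − 1) × b. The bias in the change contrast is therefore

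(r − 1) × (completers' mean baseline, intervention − control).

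Holding the total loss at 42 × (p1 + p0) = 16.8, and taking the completers' mean baseline from 2 million simulated draws:

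| Dropout, intervention / control | Baseline difference among completers (SD) | Bias = −0.4 × difference (SD) |
|---|---|---|
| 20% / 20% | 0 | 0 |
| 25% / 15% | −0.081 | 0.03 |
| 30% / 10% | −0.162 | 0.065 |
| 40% / 0% | −0.333 | 0.13 |

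A positive value means less apparent improvement in the intervention arm. If dropout is completely at random, the bias is nil.

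**6. Precision for comparison.** With 33.6 completers per arm, the SD of change is √(2 × (1 − 0.6)) = 0.894, and the standard error of the contrast is 0.894 × √(2 / 33.6) = 0.22 SD. Conditioning on baseline, the residual SD is √(1 − 0.36) = 0.80, and the standard error is 0.80 × √(2 / 33.6) = 0.20 SD. In simulation, conditioning on baseline left a bias of at most 0.001 SD under this dropout model.

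**The case against.** The strongest reply is that the article never says incomplete cases are deleted. Imputation followed by ANOVA fits its sentence, and a journal article may leave missing-data handling to a full protocol or analysis plan that is not shown. The per-protocol definition supports this reading: listing assessment completion as a restriction makes sense only if the intention-to-treat set was meant to be wider. This stands, and it makes the point conditional. A reader might infer that the trial will certainly run a completers analysis; the article does not establish that. What remains is more than silence, because the article names a method that cannot honour the stated principle without a further step, and does not state the step.

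A reader might also infer that a loss of 17 people brings a material bias. The article does not support that. It gives no dropout rate by arm, and at that loss the bias is nil with equal dropout and reaches 0.13 SD only if all the loss falls in one arm. The 25-euro incentive for completing all data entry is offered in both arms, which may limit any difference. Nor should the illustration be read as a route to a false benefit: where the more distressed drop out more often from the intervention arm, the error runs against the intervention. Dropout that depends on the 6-week outcome could push it the other way. In a run with r = 0.5 and about 27% against 15% dropout, the estimate shifted by about −0.12 SD.

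Finally, this is a pilot sized to estimate a pooled standard deviation, and its Discussion allows only preliminary conclusions on effectiveness. That limits severity, but the article still plans between-group comparisons and effect sizes from these data.

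**Conclusion.** The concern holds in conditional form. Unless missing 6-week scores are imputed first, the analysis labelled intention-to-treat covers about 67 of 84 participants at the plan's own attrition rate, and the per-protocol comparison cannot reveal an effect of dropout. These conclusions rest only on the article's figures and on how repeated measures ANOVA works.

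The bias is a possibility, not a prediction. Under the stated assumptions it ranges from 0 to 0.13 SD, or from nothing to about 0.6 of a standard error (0.13 / 0.22), and the upper end needs extreme imbalance between arms. Severity is moderate.

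**What to change.** Replace the repeated measures ANOVA in the Statistical analysis section with one of the following, both available in SPSS:
- a linear mixed model fitted by likelihood to all randomised participants, with baseline and week 6 as responses, baseline means constrained equal across arms, and the arm contrast at week 6 as the estimate; or
- multiple imputation of missing 6-week scores, followed by baseline-adjusted ANCOVA.

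Either is valid if data are missing at random given what the model includes. With only two occasions, the mixed model gains mainly by conditioning on baseline and does not recover the missing outcomes. Imputation can draw on further baseline measures.

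State that the K10 sensitivity analysis already promised will examine departures from missing at random, for example by shifting the imputed 6-week scores by a range of amounts. If an unpublished protocol already places imputation before the ANOVA, say so and describe it.

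The cost is a change of wording and a little more analysis work. Design, sample size and data collection are unaffected.
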